## Objectives

2

The objectives of this study are:

To assess the feasibility of implementing the mixed herb aromatherapy intervention in a clinical setting. Key metrics include recruitment rates, adherence rates, completion rates and safety assessment.To gather preliminary data on the efficacy of mixed herb aromatherapy on PSD, including symptom relief and improvements in the quality of life of the patients.To compare the preliminary effects of aromatherapy versus routine treatment and CBT for PSD patients, focusing on differences in symptom recovery and sustainability of treatment effects.To explore the impact of aromatherapy on brain function assessments (EEG and fNIRS) and its correlation with the recovery of patients suffering from PSD. This study will utilize EEG and fNIRS to assess the impact of aromatherapy on brain function in PSD patients and investigate the correlation between these brain function changes and the recovery progress of the patients.

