## Trial design

3

A single-blind, pilot randomized controlled trial will be conducted to evaluate the preliminary efficacy and feasibility of mixed herb aromatherapy compared to standard care and CBT. This study will enroll ninety-nine post-stroke patients with PSD at the Second Rehabilitation Hospital of Shanghai. Prior to initiating rehabilitation, demographic details of all participants, including name, gender, age, education level, and medical history, will be collected. A centralized, web-based service provided by Research Randomizer (https://www.randomizer.org/) will be utilized to generate a randomization sequence, ensuring an even distribution of patients between the three groups: the non-active control group (receiving standard care), the aromatherapy group (undergoing daily aromatherapy inhalation), and the CBT group (receiving CBT sessions twice weekly) in a 1:1:1 ratio. The intervention will last for four weeks.

Primary feasibility outcomes will include recruitment rates, adherence to the intervention and completion rates. Recruitment rates will be monitored and documented weekly. Adherence will be tracked through participant logs, ensuring that each session is recorded. Completion rates will be calculated at the study’s conclusion.

Evaluation of intervention effectiveness will be conducted at three time points: before the intervention (baseline), immediately after the intervention (four weeks), and one month post-intervention, to assess the effectiveness of the treatments (see **Figure 1** for details).

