#### Secondary outcome measures

4.3.2

Patient Health Questionnaire-9 (PHQ-9): The Chinese version of PHQ-9 has been translated and validated, demonstrating good validity and reliability for assessing depression severity among Chinese populations (42). It consists of nine items representing various aspects of depressive symptoms with high reliability and easy to understand. Each item is rated on a four-point scale, with the patient choosing the most compatible answer based on how they felt over a two-week period. 0: no problem at all; 1: a few days; 2: most of the time; 3: every day. The total score ranges from 0 to 27, with higher scores indicating more severe depressive symptoms. Score 0 to 4: no or minimal depressive symptoms; 5 to 9: mild depression; 10 to 14: moderate depression; 15 to 19: moderately severe depression; 20 to 27: severe depression.Hospital Anxiety and Depression Scale: We will use the translated and validated Chinese version of the HADS. This version has demonstrated good validity and reliability in studies involving Chinese populations (43). The self-report scale is widely used to assess patients’ levels of anxiety and depression in healthcare settings. The scale was developed by Zigmond and Snaith in 1983 and is primarily designed to be used as a quick and easy measure of a patient’s psychological state under the guidance of a non-psychological professional (44). The HADS consists of 14 items, of which 7 items are used to assess depression (Items #2, 4, 6, 8, 10, 12, and 14 items) and 7 items of the scale are used to assess anxiety (Items #1, 3, 5, 7, 9, 11, and 13). Each item has a 4-point scale, with each item scored on a scale ranging from 0 to 3, and the total score ranging from 0 to 21.Mini-Mental State Examination (MMSE): We will use the translated and validated Chinese version of the MMSE. This version has been widely applied in various studies and has proven effective and reliable for assessing cognitive function in Chinese populations (45). The MMSE is a simple instrument widely used for the assessment of cognitive functioning and consists of 30 items with a total score of 30 points. It includes attention and calculation ability (5 points), memory (3 points), orientation (10 points), language (8 points), and executive function (4 points). 0-9: moderate cognitive disorder; 10-17: mild cognitive disorder; 18-23: mild cognitive impairment; and 24-30: normal cognitive level.Pittsburgh sleep quality index (PSQI): We will use the Chinese translated version of the PSQI. The translated version has been validated and shown to be effective and reliable in assessing sleep quality among Chinese populations (46). The main purpose of the PSQI is to comprehensively assess the quality of an individual’s sleep, including sleep duration, difficulty falling asleep, sleep effect, sleep depth, number of sleep awakenings, and sleep medication use (47). It contains 7 main subscales that assess different aspects of sleep: subjective sleep quality, difficulty falling asleep, sleep duration, sleep effect, sleep depth, use of medications, and daytime dysfunction. Each subscale has a score range of 0-3 and a total score of 21, with higher scores representing poorer sleep quality. a total PSQI score of >5 is usually considered poor sleep quality.Stroke Specific Quality of Life Scale (SS-QOL): We will use the translated and validated Chinese version of the SS-QOL. This version has demonstrated good validity and reliability for assessing the quality of life in Chinese stroke patients (48). The scale includes 12 dimensions of energy, family role, language, activity, mood, personality, self-care, social role, thinking, upper limb function, vision, and work/productivity, with each entry on a 5-point scale (1 to 5). The total score ranged from 49 to 245, with higher scores indicating better quality of life.A 32-channel wireless multichannel EEG acquisition and analysis system from Xi’an ZhenTec Intelligence Technology, ZhenTec NT1, will be used for brain EEG data acquisition. Saline electrodes will be used and placed according to the international standard lead 10-20 electrode system position. The sampling rate will be 1000 Hz and electrode impedance will be kept below 10 kΩ. Resting state EEG will be recorded from the patients before and after four weeks of intervention. Resting-state EEG: EEG data will be recorded for 5 minutes in a quiet state. LZC complexity nonlinear feature extraction will be performed for the full frequency band (0.6-46Hz), δ (1-3.5Hz), θ (4-7Hz), α (8-13Hz), and β (13-30Hz) frequency bands of the resting-state EEG, respectively, to calculate the LZC values.A 64-channel fNIRS device (BS-2000L, Wuhan Znion Technology Co., Ltd., China) will be used to collect information on changes in oxygenated hemoglobin (HbO) and deoxyhemoglobin (HbR) concentrations in the prefrontal lobe and part of the temporal lobe of the subjects during the VFT task. The VFT consists of the following components: (1)A 30-second pre-task baseline period to establish a resting state, during which participants will be asked to repeat the sequence “12345” to ensure consistent starting conditions. (2)A 60-second task period divided into three 20-second segments, during which participants are asked to generate as many words as possible starting with given syllables (e.g., “ba,” “da,” “pa”). (3)A 70-second post-task baseline period during which participants will again repeat the sequence “12345” until the end of the assessment at 170 seconds. This task evaluates regional brain activity and forebrain functional network connectivity. Data preprocessing includes artifact removal and baseline correction using the moving average method. HbO and HbR integral values will be calculated by averaging data from all channels, representing the hemodynamic response during the task period.

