#### Secondary outcome analysis: clinical measures

8.1.2

- Measures such as PHQ-9, HADS, MMSE, PSQI, and SS-QOL will be summarized at each time point using descriptive statistics to observe potential effects and trends. Given the limited sample size, inferential analysis will be avoided. Instead, the focus will be on descriptive statistics and comparison with minimal important changes (MIC) to assess the clinical relevance of observed changes.

- To compare the efficacy of aromatherapy versus CBT, non-inferiority tests will be conducted to determine if the efficacy of aromatherapy is not significantly worse than that of CBT. The non-inferiority margin will be defined *a priori*, typically set at a 10% margin, indicating that aromatherapy is considered non-inferior if the difference in improvement between CBT and aromatherapy falls within this margin. If assumptions for parametric tests are violated, descriptive statistics will be used to summarize the data. This analysis will highlight the potential of aromatherapy as an effective complementary therapy.

- EEG data will be processed using a bandpass filter (0.6-46 Hz) and artifacts will be removed using Independent Component Analysis (ICA). A minimum of 4 minutes of artifact-free data will be selected for further analysis. The Lempel-Ziv Complexity (LZC) values for the full frequency band (0.6-46 Hz) and specific bands: δ (1-3.5 Hz), θ (4-7 Hz), α (8-13 Hz), and β (13-30 Hz) will be summarized at baseline, post-intervention, and follow-up within each group. Changes in LZC values over time and between groups will be explored descriptively, and the relationship between changes in LZC values and improvements in PHQ-9 scores will be examined using Pearson correlation to identify potential correlations between EEG biomarkers and clinical measures of depression. This analysis will help to understand if EEG changes can be predictive of or associated with improvements in depressive symptoms, providing preliminary insights into the neurological impacts of the interventions.

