- The fNIRS data will collect information on changes in oxygenated hemoglobin (HbO) and deoxygenated hemoglobin (HbR) concentrations in the prefrontal lobe and part of the temporal lobe during the Verbal Fluency Task (VFT). The VFT will consist of a 30-second pre-task baseline, a 60-second task period, and a 70-second post-task baseline to assess changes in regional brain activity and forebrain functional network connectivity. The fNIRS data will be preprocessed to remove artifacts, with baseline correction performed using the moving average method. The last 10 seconds of the pre-task period and the first 55 seconds of the post-task period will be used for baseline correction. Descriptive statistics will summarize the integral values of HbO and HbR across different groups and time points. Changes in HbO and HbR values over time and between groups will be explored descriptively, and the relationship between HbO values and PHQ-9 scores will be examined using Spearman’s rank correlation.

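### The brain-function plan is inconsistent on follow-up EEG, omits the fNIRS change correlation that objective 4 asks for, and averages away the regional information it says it will assess

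*Protocol article*

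**What the plan says.** **Objective.** Objective 4 (Protocol article, section 2) covers both EEG and fNIRS and is to "investigate the correlation between these brain function changes and the recovery progress of the patients".

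**EEG.** Section 4.3.2: "Resting state EEG will be recorded from the patients before and after four weeks of intervention". Section 8.1.2: LZC values "will be summarized at baseline, post-intervention, and follow-up within each group". The same bullet then relates changes in LZC to improvements in PHQ-9 by Pearson correlation. Section 3 gives the general schedule: "Evaluation of intervention effectiveness will be conducted at three time points: before the intervention (baseline), immediately after the intervention (four weeks), and one month post-intervention". It does not name EEG.

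**fNIRS.** Section 4.3.2: "HbO and HbR integral values will be calculated by averaging data from all channels". Section 8.1.2 describes the verbal fluency task as serving "to assess changes in regional brain activity and forebrain functional network connectivity". HbO and HbR changes are explored descriptively, and "the relationship between HbO values and PHQ-9 scores will be examined using Spearman" (rank correlation), with no visit named.

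**Task timing.** Section 4.3.2 lists segments of 30, 60 and 70 seconds, the last running "until the end of the assessment at 170 seconds".

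**The concern.** Objective 4 rests on the EEG and fNIRS analyses alone, so those need to match both the data collected and the question asked. Three things do not fit.

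(a) The two EEG passages cannot both be right. If section 4.3.2 is complete, the follow-up LZC summary has no data. If section 8.1.2 is right, section 4.3.2 omits a recording. This touches a primary outcome: section 4.3.1 counts participants who complete every scheduled assessment and sets an 85% threshold, so staff need to know whether a follow-up EEG is scheduled.

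(b) The fNIRS correlation uses levels where the objective asks for changes. A correlation of levels shows whether more depressed people have lower HbO. It does not show whether people whose HbO changes are the people who recover.

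(c) A single mean over all channels cannot distinguish one region from another, although regional activity is the stated purpose of the task.

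**Working it through.** **1. EEG times, side by side.**
- Section 4.3.2: before and after the four weeks, 2 recordings.
- Section 8.1.2: baseline, post-intervention, follow-up, 3 summaries.
- Section 3: 3 time points for effectiveness in general, EEG not named.
- Table 1 (section 4.4), which should settle the matter, is not visible in the text reviewed.

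Result: a contradiction over one visit. The baseline and week-4 recordings appear in both passages, so the planned correlation of LZC change with PHQ-9 improvement can be done over that interval.

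**2. fNIRS: level against change.** The two bullets of section 8.1.2 differ:
- EEG: change in LZC against improvement in PHQ-9, which matches objective 4.
- fNIRS: HbO values against PHQ-9 scores, which does not.

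To see how far the two kinds of correlation can differ, take each variable as a baseline level (SD 1) plus a change (SD k), with change independent of baseline. Let r_B be the correlation of the baselines and r_C that of the changes. The correlation of post-treatment levels is then

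r_post = (r_B + k² × r_C) / (1 + k²)

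The protocol gives none of these inputs, so k, r_B and r_C are assumptions. The negative sign follows the study cited in section 1.1, where higher HbO went with lower depression scores.

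| k | r_B = -0.5, r_C = 0 | r_B = 0, r_C = -0.5 |
|---|---|---|
| 0.5 | -0.5/1.25 = -0.40 | -0.125/1.25 = -0.10 |
| 0.7 | -0.5/1.49 = -0.34 | -0.245/1.49 = -0.16 |
| 1.0 | -0.5/2 = -0.25 | -0.5/2 = -0.25 |

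In the first column the changes are unrelated, yet the levels correlate. In the second the changes are clearly related, yet the levels correlate only weakly. A simulation at k = 0.7 gave -0.335 and -0.164, in agreement.

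**3. Precision of the replacement.** Section 4.5 plans about 30 per group before a 10% dropout allowance (30 × 1.10 = 33; 3 × 33 = 99). With about 30 analysable per arm, or 90 over three arms, the approximate Fisher-z interval is tanh(atanh(r) ± 1.96/√(n − 3)):
- n = 30: half-width around r = 0 is tanh(1.96/√27) = 0.36; an observed r = 0.30 gives -0.07 to 0.60.
- n = 90: half-width is tanh(1.96/√87) = 0.21; an observed r = 0.30 gives 0.10 to 0.48.

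The formula is for Pearson's r and only approximate for Spearman's. The estimate will be imprecise within an arm, so it should be reported with its interval.

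**4. Channels.** The 64-channel device covers the prefrontal lobe and part of the temporal lobe (section 4.3.2). Averaging all channels leaves one HbO value and one HbR value per person and visit. Neither separates the two areas, and neither can show connectivity, which needs at least two signals.

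**5. Task timing.** 30 + 60 + 70 = 160 seconds, against 170 stated. The windows used for baseline correction (last 10 s of the pre-task period, first 55 s of the post-task period) fit inside the stated 30 s and 70 s segments, so no stated analysis turns on the difference.

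**The case against.** The strongest reply is that these are secondary, exploratory outcomes of a feasibility pilot, presented in a condensed article. Section 8.1.2 avoids inference on the clinical scales and presents the EEG correlation as preliminary, and section 8.1 promises confidence intervals where applicable. Connectivity processing and the visit for the HbO correlation are details that a fuller plan may hold. All of that stands, and it limits the weight of the point. It does not remove it, because the EEG times, the level correlation and the all-channel mean are stated in the text.

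Several stronger readings are tempting but unsupported:
- **That objective 4 cannot be delivered.** Its EEG half can, from baseline to week 4. Channel averaging conflicts with the task's stated purpose, not with objective 4, which names no region.
- **That no participant will have a follow-up EEG.** This rests on one sentence in section 4.3.2. The general schedule in section 3 points the other way, and Table 1 is not visible.
- **That the HbO test has an inflated error rate because visits are pooled.** No passage says that visits will be pooled as independent rows.
- **That averaging loses a known share of the signal.** The protocol does not say how many channels respond, the device already covers a restricted area, and averaging also reduces noise.
- **That the correlations must be adjusted for arm.** This is debatable when the objective concerns how the impact of aromatherapy on brain function relates to recovery.

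**Conclusion.** The point holds as a set of inconsistencies to correct before analysis. The EEG passages disagree about one visit, and only the follow-up LZC summary and the meaning of a scheduled assessment depend on which is right. The fNIRS correlation, as written, answers a question about severity between people and leaves objective 4 without its fNIRS change-recovery analysis. The all-channel mean cannot support the regional and connectivity claims.

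The size of (b) can only be illustrated. For change SDs of 0.5 to 1.0 times the baseline SD, a level correlation of -0.40 to -0.25 can arise with no correlation of changes, and a change correlation of -0.5 can appear as -0.10 to -0.25. These figures assume that change is independent of baseline and that k is the same for both variables. Items (a) and (c) rest on the text alone. The 160 against 170 seconds is a minor slip.

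**What to change.** (a) Align sections 4.3.2 and 8.1.2 and Table 1. Either delete the follow-up LZC summary or state that resting EEG is also recorded at follow-up. Then say whether a follow-up EEG counts as a scheduled assessment for the 85% completion criterion.

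(b) In section 8.1.2, replace the HbO correlation with a Spearman correlation between the baseline-to-week-4 change in the HbO integral and the change in PHQ-9 over the same interval, one row per participant, reported with a 95% CI. This mirrors the plan's own EEG analysis. It assumes fNIRS is recorded at both visits, which the planned description of changes over time implies.

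(c) Compute the HbO and HbR integrals separately for the prefrontal and the temporal channels already recorded, or remove the claims about regional activity and connectivity.

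(d) Reconcile the segment lengths and the total duration of the task.

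The cost is revised wording, a little more processing of data already collected, and a few more exploratory estimates to report. If the follow-up LZC summary is deleted, no visit or procedure is added. If it is kept, the follow-up recording has to be in the schedule.

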### Sequence generation

5.1

Participants will be randomized in a 1:1:1 ratio to control group, CBT group or aromatherapy group. Due to the unique characteristics of each intervention, complete blinding of participants and therapists is not possible. However, measures will be taken to minimize bias, including withholding specific hypotheses about the interventions from participants. Data collection will be performed by investigators blinded to group assignments. Furthermore, data analysis will occur under blinded conditions, with assignments coded and concealed until the conclusion of the analysis.

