### Statistical methods for primary and secondary outcomes

8.1

Data analysis will be performed using SPSS 26.0. All data will be described by mean ± standard deviation (X ± S), with P < 0.05 considered statistically significant. Descriptive statistics will summarize the data. Confidence intervals and effect sizes will be reported where applicable, focusing on feasibility as the primary outcome and clinical measures as secondary outcomes.

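### The correlation of LZC change with PHQ-9 improvement has no treatment-arm term, so a pooled result can reflect arm differences rather than a patient-level link, and several bands are tested whether patients are pooled or split by arm

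*Protocol article*

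**What the plan says.** All places are in the protocol article.

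- **Method (8.1.2, EEG item).** "the relationship between changes in LZC values and improvements in PHQ-9 scores will be examined using Pearson correlation". No arm or covariate term is named, and the text does not say whether patients are pooled or analysed by arm.
- **Measures (8.1.2).** "The Lempel-Ziv Complexity (LZC) values for the full frequency band (0.6-46 Hz) and specific bands" δ, θ, α and β: five LZC measures, none designated as lead.
- **Intended reading (8.1.2).** "This analysis will help to understand if EEG changes can be predictive of or associated with improvements in depressive symptoms".
- **Significance rule (8.1).** A general line covers the analysis: "with P < 0.05 considered statistically significant". The same paragraph says that confidence intervals and effect sizes will be given where applicable. No multiplicity rule is stated.
- **Design (5.1).** "Participants will be randomized in a 1:1:1 ratio to control group, CBT group or aromatherapy group".
- **Objective (section 2).** The fourth objective includes a plan to "investigate the correlation between these brain function changes and the recovery progress of the patients".
- **EEG occasions.** Section 4.3.2 says "Resting state EEG will be recorded from the patients before and after four weeks of intervention", whereas 8.1.2 says that LZC values "will be summarized at baseline, post-intervention, and follow-up within each group".
- **Companion analysis (8.1.2, fNIRS item).** HbO is related to PHQ-9 by a Spearman correlation, also without an arm term.

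**The concern.** The clinical interest is whether a patient whose EEG changes more also recovers more. In a three-arm trial, a plain correlation of two change scores mixes that patient-level association with between-arm differences. Suppose an active treatment lowers PHQ-9 and, by a separate route, shifts LZC. The pooled correlation is then non-zero although LZC change says nothing about recovery within any arm. This can arise in the very situation the trial hopes to see, where treatment affects both mood and brain measures.

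The protocol's own background (1.1) shows why the level of analysis matters. It reports an earlier LZC study with no significant correlation with overall depression level among patients with post-stroke depression, but a significant one among stroke patients taken together. Other explanations are possible, such as a narrower range of scores among the depressed patients. Still, a plain Pearson coefficient could not separate the two.

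At stake is the interpretation of the EEG findings. An arm difference could be reported as a patient-level marker, or one chance band among several could be singled out.

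**Working it through.** **The plan's own figures.** Section 4.5 takes 30 per group and 10% dropout: 30 × 1.10 = 33 per group, and 3 × 33 = 99. This reproduces. The check therefore uses both 30 per arm (90 analysed) and 33 per arm (99 analysed). The protocol gives no power, error rate or count of tests for the correlation.

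**Assumptions.** Both change scores are normal with within-arm SD 1, the within-arm correlation is 0, and tests are two-sided at 0.05 (the protocol does not state sidedness). Two arms differ from the third by d SD on both variables. The protocol gives no value for d, so a range is shown.

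**Step 1: induced correlation if pooled.** Arm means (0, d, d) have variance 2d²/9. The between-arm covariance is the same, so r = (2d²/9) / (1 + 2d²/9).

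- d = 0.3: 0.020 / 1.020 = 0.02
- d = 0.5: 0.0556 / 1.0556 = 0.053
- d = 0.8: 0.1422 / 1.1422 = 0.125
- d = 1.0: 0.2222 / 1.2222 = 0.182

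**Step 2: rejection rate of the pooled test.** Simulation, 20,000 trials per setting:

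| d (SD, both variables) | 30 per arm | 33 per arm | Arm-adjusted |
|---|---|---|---|
| 0 to 0.3 | about 5% | about 5% | about 5% |
| 0.5 | 8% | 8% | about 5% |
| 0.8 | 21% | 24% | about 5% |
| 1.0 | 42% | 45% | about 5% |

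- One arm shifted against the other two gives practically the same rates.
- A graded shift (0, d/2, d) gives less: 15-16% at 0.8 SD and 27-30% at 1.0 SD.
- With a shift of 0.8 SD on one variable only, the rate is about 5%. The problem needs arms that differ on both.
- The arm-adjusted (within-arm-centred) correlation rejects in 4.8-5.4% of trials in every setting.

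**Step 3: analytic cross-check.** By Fisher's z with n = 99, the test statistic has mean artanh(r) × √96.

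- d = 0.8: 0.1252 × 9.798 = 1.23, giving a rejection probability of 23%
- d = 1.0: 0.1839 × 9.798 = 1.80, giving 44%

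Both agree with the simulation.

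**Step 4: number of tests.** For k independent tests, the chance of at least one false positive is 1 − 0.95^k.

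- Pooled: k = 5, 1 − 0.95^5 = 22.6%. Correlated bands lower this, to about 18% at an assumed between-band correlation of 0.5.
- By arm: k = 5 × 3 = 15, 1 − 0.95^15 = 53.7%, with 15 × 0.05 = 0.75 false positives expected. Simulation at 30 per arm gives about 46% at between-band correlation 0.5 and 34% at 0.8.
- Fifteen is a minimum. It follows from one change score per band, as in 4.3.2. If follow-up LZC is also correlated, as 8.1.2 would allow, k = 30 and 1 − 0.95^30 = 78.5%.

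**The case against.** **The plan is silent on pooling, and a fuller document may settle it.** That is fair as far as it goes. But a choice between pooled and by-arm analysis does not cure a bivariate method. Pooled, it is open to arm-driven correlation; by arm, it triples the tests. An arm term would change the method stated in 8.1.2, so this is more than an omitted detail.

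**The pooled rejection is not strictly an error.** This stands. In the scenarios above the marginal correlation really is non-zero, so the test rejects a false null. A reader might infer that the Pearson test is invalid; it is not. The fault lies in reading a marginal correlation as a patient-level link. One may also argue that arm-driven co-movement is part of what the fourth objective wants. The between-group descriptions of LZC and PHQ-9 already show that component, and the correlation adds something distinct only if arm is held fixed.

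**The work is exploratory.** This also stands, and it limits severity. Section 4.5 puts feasibility ahead of hypothesis testing, and 8.1.2 calls the EEG insights preliminary. However, the sentence on avoiding inference sits in the item on the clinical scales, and the next item prescribes non-inferiority tests. It therefore does not clearly govern the EEG item, and the general significance rule in 8.1 remains.

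**The shifts are assumed.** Correct. Nothing in the protocol suggests that LZC will move by 0.8 SD, and at 0.5 SD or less the inflation is small.

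**Conclusion.** The point holds in a limited form. An unadjusted correlation in a three-arm trial cannot tell a patient-level association from arms that differ on both measures. Under zero within-arm correlation, the pooled test rejects in about 8% of trials at 0.5 SD, 21-24% at 0.8 SD and 42-45% at 1.0 SD, and near 5% otherwise. These rates rest on assumed equal shifts in both variables, normal data and two-sided testing. Multiplicity is present on either reading: 5 tests if pooled, at least 15 if by arm.

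Two stronger readings are not supported. A reader might infer that a full-scale trial would be built around a spurious EEG band. No section says so: 4.3 and 4.5 tie that decision to the feasibility criteria. A reader might also infer that the fourth objective rests on this correlation alone. The descriptive LZC and fNIRS comparisons and the HbO correlation serve it too.

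Severity is minor to moderate.

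**What to change.** In 8.1.2:

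1. Replace the plain Pearson correlation by one arm-adjusted analysis per band: a partial correlation of LZC change with PHQ-9 change given arm, or a regression of PHQ-9 change on LZC change with arm indicators.
2. Treat the HbO and PHQ-9 Spearman correlation in the same way, as a partial rank correlation given arm.
3. Report all band results as exploratory estimates with 95% confidence intervals, without a significance label, unless one band is named in advance as lead. Which band leads is the investigators' choice.
4. Reconcile 4.3.2 and 8.1.2 on whether EEG is recorded at follow-up, so that the number of change scores per band is fixed.

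The cost is a few sentences, no new data, and 2 degrees of freedom (97 to 95 with 99 patients).

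### The post-task fNIRS baseline starts the moment the task ends, so it can contain the tail of the response that the HbO/HbR integral is meant to measure

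*Protocol article*

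**What the plan says.** Section 8.1.2 (Secondary outcome analysis: clinical measures) of the protocol article describes the verbal fluency recording as "a 30-second pre-task baseline, a 60-second task period, and a 70-second post-task baseline". It fixes the correction windows to the second: "The last 10 seconds of the pre-task period and the first 55 seconds of the post-task period will be used for baseline correction". The method is named only in general terms: "with baseline correction performed using the moving average method". Neither section states how the pre-task and post-task windows are combined into one baseline.

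Section 4.3.2 (Secondary outcome measures) defines the derived quantity: "HbO and HbR integral values will be calculated by averaging data from all channels, representing the hemodynamic response during the task period". It also describes the closing segment: "A 70-second post-task baseline period during which participants will again repeat the sequence “12345” until the end of the assessment at 170 seconds".

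The integrals are then used in two ways in section 8.1.2. First, "Changes in HbO and HbR values over time and between groups will be explored descriptively". Second, "the relationship between HbO values and PHQ-9 scores will be examined using" Spearman's rank correlation. No other section inserts a recovery interval, gives a recovery time or replaces the 55 s window.

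**The concern.** The integral is meant to describe the response during the 60 s task. A haemoglobin response that returns to baseline gradually is still present in the first seconds after the task. A baseline window that opens at task end averages that residue in, and subtracting it removes part of what is being measured. For HbR, where the change may be negative, the equivalent is a shift of the integral towards zero. The pre-task 10 s dilute the effect but do not cancel it. A moving average smooths a trace; nothing in the text suggests that it separates residual response from baseline.

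The loss depends on how slowly each patient recovers. Two patients with the same task activation but different recovery would receive different integrals, and a change in recovery speed between visits or arms could be read as a change in activation. The integral is the only fNIRS quantity whose derivation the article describes, and it supplies the fNIRS part of the fourth objective.

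**Working it through.** **Timeline.** 30 + 60 + 70 = 160 s. Section 4.3.2 says the recording runs "until the end of the assessment at 170 seconds", so the plan's own total is not reproduced. The 55 s window is counted from task end, so this conflict does not move it. It does affect what remains afterwards: 70 − 55 = 15 s as stated, or 80 − 55 = 25 s if the missing 10 s belonged to the post-task period.

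**Model (assumed; the documents give no response shape).** Unit plateau, exponential rise with constant 8 s during the task, exponential decay with constant τ afterwards, no noise, no undershoot. Time is in seconds.

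- Task integral against the pre-task level: 60 − 8(1 − e^(−60/8)) ≈ 52.0.
- Mean residue in the first 55 s after the task: m ≈ (τ/55)(1 − e^(−55/τ)).
- Straight line between window means: the window centres are 5 s before task start and 87.5 s after it. At mid-task (30 s) the post-task mean has weight 35/92.5 = 0.378. Loss = 60 × 0.378 × m.
- Pooled mean of all baseline samples: the post-task weight is 55/65 = 0.846. Loss = 60 × 0.846 × m.

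Example, τ = 10 s: m = 0.181. Line: 60 × 0.378 × 0.181 = 4.1, and 4.1/52.0 = 7.9%. Pooled: 60 × 0.846 × 0.181 = 9.2, and 9.2/52.0 = 17.7%.

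**Late window, 55 to 70 s after the task.** The mean residue is (τ/15)(e^(−55/τ) − e^(−70/τ)). The line weight is 35/127.5 = 0.275 and the pooled weight is 15/25 = 0.6.

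| τ (assumed) | m, 0–55 s | Loss, line | Loss, pooled | Late window, line | Late window, pooled |
|---|---|---|---|---|---|
| 5 s | 0.09 | 4.0% | 8.9% | 0% | 0% |
| 10 s | 0.18 | 7.9% | 17.7% | 0.1% | 0.1% |
| 15 s | 0.27 | 11.6% | 25.9% | 0.5% | 1.1% |
| 25 s | 0.40 | 17.6% | 39.4% | 2.6% | 5.8% |
| 30 s | 0.46 | 20.0% | 44.7% | 4.0% | 8.7% |

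A rise constant of 6 s gives nearly the same losses (for example 7.6% and 17.1% at τ = 10 s).

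**Between-patient effect under this model.** Same task response, τ = 25 s against 10 s. Line: (1 − 0.176)/(1 − 0.079) = 0.895, about 11% lower. Pooled: (1 − 0.394)/(1 − 0.177) = 0.736, about 26% lower. Both recovery constants are assumptions.

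**Other shapes.** A gamma response peaking at 5 s loses 3 to 5% (line) or 7 to 10% (pooled). A double-gamma response with its small undershoot loses 2.9% or 6.6%. Adding a larger undershoot to the exponential model (rise constant 6 s) reverses the sign: about +0.6 to +4% at 0.3 of plateau, and +10 to +22% at 0.5. The late window is not error-free there either. At 0.3 it gives about +1.6 to +4%, no better than the planned window, in which decay and undershoot happen to cancel. At 0.5 it gives +2.7 to +6%.

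**Noise cost of the late window.** For independent noise, the SD of the window mean rises by √(55/15) = 1.9. With autocorrelated noise (assumed time constants 0.5 to 10 s) the factor is about 1.5 to 1.9. For the line-corrected integral with independent unit noise per second:

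- Planned window: variance = 60 + 3600(0.622²/10 + 0.378²/55) ≈ 208.
- Late window: variance = 60 + 3600(0.725²/10 + 0.275²/15) ≈ 268.
- SD ratio: √(268/208) ≈ 1.13. Allowing for autocorrelation, the rise is roughly 12%.

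With a pooled mean the ratio is √((60 + 3600/25)/(60 + 3600/65)) = √(204/115.4) ≈ 1.33.

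**The case against.** The strongest reply is that the size is not knowable from the article. It gives no recovery time and no rule for combining the windows, and the larger losses need recovery three to four times slower than the assumed rise. With rise and recovery both at 8 s the loss is about 6% (line) or 14% (pooled), and gamma-type shapes give less. That stands, and it is why only a conditional range can be given. The missing combination rule is a detail that an article may leave to a fuller document, so it is not held against the plan. A reader should also not infer that a straight line is planned; it is one possible reading.

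Second, the same window applies to every arm and visit. A common proportional loss would leave relative changes and rank correlations untouched. That also stands: distortion needs recovery to differ between patients, visits or arms, and whether it would reorder patients enough to alter the Spearman coefficient has not been shown.

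Third, the impact is limited. The integrals are secondary and descriptive, no feasibility criterion uses them, and the fourth objective also draws on EEG complexity, which has its own analysis.

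None of this removes the defect. The window is stated exactly, not left open, and it overlaps the period in which the measured response would still be subsiding.

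**Conclusion.** The point holds in a limited form. The stated post-task window begins at task end and can include residual task response, while 15 s of later recording go unused. For exponential recovery with assumed constants of 5 to 30 s and no large undershoot, the integral is reduced by about 4 to 20% with a line or 9 to 45% with a pooled mean; gamma-type responses give about 3 to 10%.

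Two stronger readings are tempting and not supported. One is that the integral always shrinks: a large undershoot would reverse the sign. The other is that the comparisons and the correlation with PHQ-9 are distorted: they can be, if recovery varies, but the documents contain nothing that shows it does. The 160 s against 170 s conflict is a separate error of description. It does not unsettle the planned window, but it must be resolved before a window at the end of the period has a fixed position.

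**What to change.** In section 8.1.2, treat the first 55 s after the task as recovery. Take the post-task baseline from the end of the post-task period (the last 15 s of the stated 70 s) and combine it with the last 10 s before the task, for example by a straight line between the two window means. Say how the windows are combined, and what the moving average is for.

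In section 4.3.2, make the segment lengths and the stated end of the recording agree, and use the same event marks in the analysis.

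The cost is a wording change and one setting in the processing, applied to data the protocol already records. The statistical price is noise: the 15 s mean is about 1.5 to 1.9 times as noisy as the 55 s mean, which raises the noise SD of a line-corrected integral by roughly 12%. A pooled mean would pay more (about 33% for independent noise), which favours the line. The original window could be kept as a sensitivity analysis to show how much the choice matters.
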